### Component 4: validation study using 24-hour urinary sodium

A 10% sub-sample from ‘
*Component 3*’, described above, will be asked to provide a 24-hour urine sample to measure 24-hour urine sodium excretion to assess the accuracy of spot urine sodium estimation and the correlation between spot urinary sodium and 24-hour urinary sodium. The sub-sample will consist of participants from the first six EDs to be recruited for the survey in ‘
*Component 3*’. All participants from these first six EDs will be included. We will exclude participants who are unwilling to carry out the 24-hour urine collection. If we have less than 120 participants from the first six EDs, we will continue to recruit from the next EDs until the targeted sample of 120 individuals is reached. We will estimate 24-hour urine sodium from the spot urine sodium and then assess the levels of agreement between 24-hour urine sodium estimated from spot urinary sodium and 24-hour urinary sodium from the 24-hour urine sample. Data from this validation study will be used to calibrate equations for estimating 24-hour urinary sodium from spot urinary sodium measurements. These new equations from local data may then be used for this and future studies on urine sodium excretion.

The procedure for collecting 24-hour urine sample will be as follows: On the morning of the start of the 24-hour period, the participant must urinate to completely empty the bladder and record the start time. This “first-pass urine” is discarded. Subsequently all urine passed is collected in a container, including the first urine of the following morning. This should be at the same time as the previous morning to ensure 24 hours is completed. The time the final urine sample is passed is recorded. The container with the 24-hour urine sample will be collected from the participant later that morning. The information sheet for the 24-hour urine collection can be found as
*Extended data.*
^
42
^

After the samples have been collected, we will assess we will assess urine volume, measure urine sodium concentration, urine potassium concentration and urine creatinine. We will exclude participants whose 24 hour urine volume is <500 ml or collection time is <22 hours; we will also exclude participants whose 24 hr urine creatinine is greater than 2SD above or below the sex-specific mean (Du et al 2021). Where collection time is shorter or longer than 24 hours, we will adjust the volume to 24-hours by dividing the total volume by collection time (in hours) and multiplying by 24 (Jackson et al 2020).

*Sample size and power*

Sample size calculations were estimated using the
*‘power onecorrelation’* command in Stata. Estimated correlation coefficients for spot urinary sodium compared to 24-hour urinary sodium were obtained from Brown
*et al.*,
^
23
^ and Tanaka
*et al.*,
^
21
^ using data from Western and Japanese participants in the INTERSALT study. Estimated correlation coefficients were 0.46 for men and 0.34 for women in the study by Brown
*et al.*, and 0.65 for men and women combined in the study by Tanaka
*et al*. Using 0.40 and 0.65 as the null and alternate estimates, yield as sample size of 67. If we went for a slightly more precise estimate of 0.4 and 0.60, the required sample size would be 112 participants. The targeted 120 participants should be adequately powered to assess correlations between spot and 24-hour urine sodium in this study.

*Statistical analyses*

Agreement between different measures of dietary sodium consumption will be computed using the intra-class correlation coefficients and Bland-Altman plots. We will assess whether physical activity level is associated with 24 hour or spot urine sodium and adjust accordingly. We will also classify participants as high salt consumption based on WHO recommended values and assess the level of agreement between classification based on the spot urine sodium and 24-hour urine sodium using the kappa statistics.

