*i.e.*, 2,656 vs. 2,457), the required sample size with alpha 0.05 and power 80% was estimated as 511. Given the design effect of 1.94 as calculated above, the minimum sample size accounting for survey design would be 991. We will target a sample size of 1,200 participants (20% above the minimum sample size) to allow for participant non-response and missing data.

*Data management*

Data will be collected by trained data collectors using password-protected tablet computers, with
REDCap (RRID:SCR_003445) data collection software. We will include range and consistency checks to minimize data entry errors. Data collected on the tablets will be protected using data encryption. Options to transfer data to external drives (
*e.g.*, USB flash drives and SD cards will be disabled. Data will then be uploaded to a secure server using data encryption protocols. Deidentified data will then be downloaded for analysis. Access to data will be limited only to members of the study’s data analysis team. De-identified data will be kept indefinitely. Identifiable data, such as consent forms will be kept on secure encrypted servers and will be destroyed by permanent deletion from the server after five years. To assess data accuracy and reliability of data, we will have project staff recollect data from 5–10% of respondents to check against the original collected data.

*Statistical analyses*

From these data we will estimate the proportion of participants reporting appropriate knowledge on the effects of salt on health, and the proportion of participants with various attitudes and practices regarding salt intake. We will also obtain mean urine sodium concentration and estimate 24-hour urine sodium using the PAHO (Equation 1) equations. We will also explore the development of a new equation for use in Jamaica and similar populations from our validation study in ‘

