### Ethical considerations

The study will be conducted in full compliance with international ethical standards as well as the Mona Campus Research Ethics Committee and Ministry of Health Advisory Panel on Ethics and Medico-Legal Affairs guidelines for the conduct of research. Ethical approval for the study was obtained from the University of the West Indies Mona Campus Research Ethics Committee (study number: CRECMN.153 2020/2021; approved August 17, 2021) and the Ministry of Health and Wellness Advisory Panel on Ethics and Medico-Legal Affairs (study number: 2021/05; approved August 25, 2021).

This is a minimal risk study, involving analyses of previously collected data, questionnaires on non-sensitive subjects and non-invasive measurements. Participants will provide written informed consent or witnessed verbal consent, given the limitation of face-to-face contact due to COVID-19. Where face-to-face contact is necessary, we will observe appropriate precautions, including wearing of masks and hand sanitization. Data will be stored on password-protected computers or tablets, or in locked filing cabinets, and treated with strict confidentiality. Each study participant will be given a unique study identification number that will be recorded on the consent forms and data collection records. Consent forms will be kept separately from the data collection records to protect participants identity. There are no direct benefits to the participants, except for receiving information on blood pressure, body size, and the effects of salt on health. Participants will be selected based on their residence in randomly selected communities and not because of easy availability or diminished autonomy. The restaurant owners or managers will also provide written or verbal informed consent.

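### Component 4 takes its validation and calibration sample from the first six EDs in field order, with no random choice stated, so agreement results and any local equation rest on a few whole clusters

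*Protocol article*

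**What the plan says.** Component 3 draws 60 EDs from all 14 parishes with probability proportionate to size, then 20 households per ED and one adult per household.

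Component 4 takes a 10% sub-sample of this survey. Its section fixes the choice in four statements:

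- "The sub-sample will consist of participants from the first six EDs to be recruited for the survey".
- "All participants from these first six EDs will be included".
- "We will exclude participants who are unwilling to carry out the 24-hour urine collection".
- If fewer than 120 are obtained, "we will continue to recruit from the next EDs until the targeted sample of 120 individuals is reached".

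The same section gives the sample a second job besides assessing agreement: "Data from this validation study will be used to calibrate equations for estimating 24-hour urinary sodium from spot urinary sodium measurements". It adds: "These new equations from local data may then be used for this and future studies on urine sodium excretion". The Component 3 analysis paragraph names the PAHO equation for estimating 24-hour sodium and then says: "We will also explore the development of a new equation for use in Jamaica and similar populations from our validation study". Objective 4 is framed for the Jamaican setting as a whole.

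**The concern.** The 60 EDs are a probability sample. The six worked first are a probability sub-sample only if the order of work was randomised, and the article does not say that it was. The top-up rule follows the same order, and people unwilling to do the 24-hour collection are replaced by people from later EDs.

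Two things are at stake. The first does not depend on which equation is finally used. The ICC, Bland-Altman and kappa results for Objective 4 describe a handful of whole clusters. If the relation between spot and 24-hour sodium differs by area, season or field team, those results need not hold for Jamaica. One possible route is in the plan itself: the Component 3 spot sample may be an early-morning or a casual one, and that mix could vary between EDs.

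The second is conditional. If a local equation fitted on these people replaces PAHO in Component 3, the same difference becomes a bias in the national mean. The error of the fitted equation also becomes part of the error of that mean.

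**Working it through.** **Coverage.** 6/60 = 10% of EDs, and at most 6 of 14 parishes. 6 × 20 = 120, so a single unwilling participant triggers the top-up, which may add a few more EDs in field order.

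**The plan's own figures.** The Component 4 sizes come from n = [(1.960 + 0.842)/(atanh r1 − atanh r0)]² + 3, taking two-sided alpha 0.05 and power 80%:

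- r0 = 0.40, r1 = 0.65: 66.5, rounded up to 67, as stated.
- r0 = 0.40, r1 = 0.60: 111.1, rounded up to 112, as stated.

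Both reproduce, and both treat people as independent. In Component 3 the plan does allow for clustering: 511 × 1.94 = 991.

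**SD of 24-hour sodium.** The article gives none, so it is solved from the Component 3 sample size (2,656 vs 2,457, a difference of 199 mg; n = 511; power 80%):

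- Normal approximation: 199 × √511 / 2.802 = 1,606 mg. The one-sample t-test gives 1,603 mg.
- Component 1 (266 mg, n = 563, power 97.5%) gives 1,610 mg and 1,607 mg in the same way.

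About 1,600 mg is therefore the planning value; 1,603 is used below. That it is also the SD of measured 24-hour sodium is an assumption.

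**Calibration error in the mean level, if a local equation is used.** Take r = 0.6, one of the plan's own alternatives.

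- Residual SD = 1,603 × √(1 − 0.36) = 1,282 mg.
- Half-width, independent people: 1.96 × 1,282/√120 = 229 mg (8.6% of 2,656).
- Half-width at design effect 1.94: 229 × √1.94 = 320 mg (12.0%).

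**Survey sampling error in Component 3.** 1.96 × 1,603 × √(1.94/1,200) = 126 mg.

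**Both together.** √(229² + 126²) = 262 mg, about twice 126. With 320 mg it is √(320² + 126²) = 344 mg.

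**Range over the correlations that the article cites (half-widths in mg).**

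| r | Independent | Design effect 1.94 |
|---|---|---|
| 0.34 | 270 | 376 |
| 0.40 | 263 | 366 |
| 0.60 | 229 | 320 |
| 0.65 | 218 | 304 |

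**Effect of spreading the same 120 people.** The design effect is 1 + (m − 1) × ICC for m people per ED. The ICC of the calibration residuals is not known, so a range is assumed (r = 0.6, half-widths in mg).

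| ICC | 20 per ED: design effect | Half-width | 2 per ED: design effect | Half-width |
|---|---|---|---|---|
| 0.01 | 1.19 | 250 | 1.01 | 231 |
| 0.05 | 1.95 | 320 | 1.05 | 235 |
| 0.10 | 2.90 | 391 | 1.10 | 241 |

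These half-widths use 1.96. With six EDs there are about 5 degrees of freedom (t = 2.57), which would take 320 mg to 320 × 2.57/1.96, about 420 mg. They also leave out error in the slope, which adds to them where the validation EDs differ from the rest in mean spot sodium.

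**The case against.** The strongest reply is that PAHO is the named equation for Components 1 and 3. The local equation is to be explored and only may be used. That stands. A reader might infer that this sub-sample drives the national estimate, but the article does not support this. The national-mean figures above apply only if the local equation is adopted.

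A reader might also see a contradiction with the Ethical considerations section: "Participants will be selected based on their residence in randomly selected communities and not because of easy availability or diminished autonomy". There is none. All 60 EDs are randomly selected, so every Component 4 participant lives in a randomly selected community. The weakness lies in how EDs are sub-sampled, not in how people are approached.

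It is tempting to add that the first EDs lie close together, or that the teams are still learning. Nothing in the article says so; it describes trained data collectors and supervised recruitment. Nor does it say that a new equation's agreement would be judged on the people used to fit it. It gives no number of predictors either, so loss of accuracy in new people cannot be put in figures.

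The inputs are open to challenge as well. The 1.94 was estimated for urinary sodium in JHLS-III and may not hold for calibration residuals; hence the ranges. An article may leave cross-validation and error propagation to a fuller document, so their absence is not counted here. The choice of EDs is different: this text fixes it.

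**Conclusion.** The point holds as a design weakness with a conditional consequence. As written, Objective 4 and any local equation rest on about six whole clusters taken in field order, with no stated randomisation. Bias arises only if the spot-to-24-hour relation varies by area, season or team; the article gives no evidence either way. If the ED order was in fact randomised, the selection part falls away, but the loss of precision from few clusters remains.

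If the local equation is used nationally, its calibration half-width would be about 229 mg (independent people) to about 320 mg (design effect 1.94). That exceeds the 126 mg from survey sampling, and an interval that left it out would be too narrow by a factor of about two or more. This rests on an SD of about 1,600 mg, r = 0.6, and a design effect that is not known for this step. The matter should be settled before any local equation is used for a national figure.

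**What to change.** **Where fieldwork still allows.** Draw the validation EDs at random from the 60, or spread the same 120 people over the EDs, about two in each. Spreading also recovers most of the precision lost to clustering. The cost is wider logistics for delivering and collecting 24-hour containers.

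**If the six EDs are already complete** (the Study status section says field work for Components 3 and 4 has begun):

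1. State how the order of the EDs was set.
2. Keep PAHO as the primary equation for Components 1 and 3, and say so explicitly.
3. Treat any local equation as a sensitivity analysis, assessed by leave-one-ED-out cross-validation.
4. Use ED-level (cluster) bootstrap errors for agreement and calibration, and carry them into any Component 3 estimate that uses the local equation. With so few clusters, present these errors as approximate.
5. Compare the validation EDs with the remaining EDs on the Component 3 data, including spot sodium and whether the sample was early-morning or casual, if recorded.

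The second route needs no new participants and little extra analysis. Its cost is wider intervals.

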^ Stroke and ischemic heart disease (IHD) mortality were reduced by 36% over the same period; it was estimated that approximately 30% of the reduction in stroke and 20% of the reduction in IHD were attributable to the reduction in salt intake.
^
8
^

The population approach as a strategy to achieve sodium reduction is supported by recommendations from the World Health Organization (WHO) and Pan American Health Organization (PAHO).
^
2
^
^,^
^
13
^ Key components of the strategy recommended by WHO and PAHO include public education programs, standardized food labelling, gradual reduction of salt content in processed foods and national surveillance systems to identify salt intake levels and major sources of salt intake. It is widely believed that population-based approaches are required to achieve the desired salt reduction, as most dietary salt consumption comes from processed foods and foods prepared outside the home, rather than by adding salt at the table.
^
2
^
^,^
^
13
^

In addition to the population-based strategies mentioned above, several studies have shown that individual-level and community-based interventions, including salt substitution, education on salt reduction strategies, use of digital platforms and electronic education materials are effective in reducing blood pressure and cardiovascular disease.
^
14
^
^–^
^
17
^ Of note, Aliasgharzadeh
*et al*. found that multicomponent interventions may be more effective than single component interventions.
^
16
^

Measurement of sodium intake in populations is challenging. Measures include dietary assessment and measurement of urinary sodium excretion.
^
18
^ Dietary sodium assessment requires significant time commitments, often underestimates sodium consumption, and is considered by some to be unsuitable for measuring population sodium intake.
^
18
^ Currently, 24-hour urinary sodium excretion is considered the gold standard method for assessment of sodium consumption.
^
18
^
^–^
^
20
^ This procedure is appropriate, given that approximately 90% of consumed sodium is excreted in the urine.
^
18
^ The 24-hour urine collection is still challenging to accomplish in large population-based studies, resulting in some studies estimating 24-hour urine excretion from a spot urine specimen.
^
18
^
^–^
^
20
^ A number of formulae have been published for estimating 24 hour urine sodium excretion from spot urine specimens, including the Tanaka formula,
^
21
^ the Kawasaki formula
^
22
^ the INTERSALT formula,
^

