23
^ and the PAHO formula.
^
13
^ A recent systematic review and meta-analysis found that estimates of mean population sodium intake from spot urine samples can provide a good indication of overall population salt intake with excellent sensitivity and specificity.
^
20
^

Globally, salt consumption is much higher than recommended. In 2010, global mean sodium intake was 3.95 g/day, with intake in men being approximately 10% higher than in women.
^
24
^ Intakes were highest in East Asia, Central Asia and Eastern Europe and lowest in sub-Saharan Africa and Latin America.
^
24
^ In the United States mean sodium intake was approximately 3.6 g/day and exceeded the recommended daily intake of 2.3 g/day for all age groups except for those 2-3 years old.
^
25
^ Data from the Health of the Nation Study in Barbados showed that mean sodium intake was 2.7 g/day, with intakes higher in men and young people.
^
26
^ Approximately 67% of individuals exceeded the WHO recommended limit of 2.0 g/day.
^
26
^

There are very little data on salt consumption patterns among Jamaicans, but it is generally believed that salt consumption is high. This is due to frequent consumption of salted meats (
*e.g.*, salt fish, salt mackerel, salted pork) in popular local dishes, frequent consumption of canned foods (such as corned beef), and frequent intake of fast foods, which are often high in salt content. Data from the 1990s provide some evidence for high salt consumption in Jamaica. In the Sodium Reduction Trial (SORT), baseline sodium excretion was found to be 149 mEq/day (3,437 mg/day) among a sample of 56 patients.
^
27
^ Additionally, the Spanish Cohort Study reported estimated sodium excretion of 3.3 g/24 hour,
^
28
^ but no recent or national estimates are available. More recently, data from JHLS-III found that among urban participants only 52% were classified as having a low salt diet, defined as no added salt at the table and infrequent consumption of processed foods.
^
29
^

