In keeping with the recommendations of WHO and PAHO and consistent with Caribbean Community (CARICOM) recommendations and a mandate of the Ministry of Health and Wellness in Jamaica, we propose the implementation of a national salt reduction program in order to reduce blood pressure and associated CVD. The program will be aligned with the overall Ministry of Health’s National Strategic and Action Plan for Prevention and Control of Non-Communicable Diseases (NCDs) and the mandate of the Food Industry Task Force. Implementation of a national salt reduction program and achieving the desired effect of reduced blood pressure and associated CVD will require a sequence of actions including the steps included in the WHO SHAKE Technical Package for Salt reduction Program. These strategies include: (i) “measure and monitor salt intake” in the population; (ii) “promote reformulation of foods and meals to contain less salt”; (iii) “implement standards for effective and accurate labelling and marketing of food”; (iv) “educate and communicate to empower individuals to eat less salt”; and (v) creating “support settings to promote healthy eating”.
^
2
^

Jamaica has adopted the global target set by WHO to reduce salt consumption by 30% by 2025. However, Jamaica does not have any baseline data on current salt consumption and therefore would be unable to indicate whether these targets are being met. Additionally, Jamaica does not any available data on salt content in restaurant foods, but a previous study had collected data on sodium content in packaged foods.
^
30
^

The objectives of this study are as follows:
1.
**Objective 1:** To estimate dietary sodium consumption among Jamaicans using spot urinary sodium analyses.2.
**Objective 2:** To assess the use of sodium in the preparation of restaurant foods and estimate the sodium content in restaurant foods.3.
**Objective 3:** To conduct a baseline survey on current knowledge, attitudes, and practices regarding salt intake in Jamaica, and estimate current levels of salt consumption. We will also evaluate associations between knowledge and attitudes regarding salt consumption and actual estimated salt consumption, dietary and other health behaviors, and health characteristics including, blood pressure and body mass index.4.
**Objective 4:** To evaluate the accuracy of spot urine sodium as a measure of dietary sodium intake in the Jamaican setting by comparing estimates to 24-hour urinary sodium excretion.

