*Component 4*’, outlined below. We will then estimate the proportion of patients with high dietary sodium consumption. We will also evaluate how dietary sodium consumption, knowledge, attitudes and practices vary by sex, other sociodemographic factors, and biomedical characteristics, including blood pressure levels and hypertension awareness. The analyses for the evaluation of knowledge attitudes and practices will be primarily descriptive, but we will use scores to classify persons in KAP categories. These categories will be created in the analysis phase of the study. Multivariable regression models will be used to identify factors associated with high sodium intake and with good knowledge, attitudes, or practices related to salt intake. Analyses will be weighted to account for survey design.

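### Component 4 plans only kappa for the high-intake classification, and kappa cannot show whether spot urine over-calls or under-calls high intake against the 24-hour reference

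*Protocol article*

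**What the plan says.** Objective 4 in the Introduction is "To evaluate the accuracy of spot urine sodium as a measure of dietary sodium intake in the Jamaican setting", by comparison with 24-hour excretion. The Component 4 section repeats the aim: "to assess the accuracy of spot urine sodium estimation and the correlation between spot urinary sodium and 24-hour urinary sodium". The Introduction also fixes which method is the reference, since "24-hour urinary sodium excretion is considered the gold standard method for assessment of sodium consumption".

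The Component 4 statistical analyses have two parts. For the continuous values, agreement "will be computed using the intra-class correlation coefficients and Bland-Altman plots". For the binary outcome, the team will "classify participants as high salt consumption based on WHO recommended values" and then "assess the level of agreement between classification based on the spot urine sodium and 24-hour urine sodium using the kappa statistics". Component 4 names no sensitivity, specificity, predictive value or comparison of the two proportions.

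The classification is also a survey result. In Component 3, after 24-hour sodium has been estimated from spot urine, "We will then estimate the proportion of patients with high dietary sodium consumption". Component 1 reports the same kind of proportion.

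**The concern.** Kappa suits two raters of equal standing. Here one classification is the reference, and the useful question is which way the other one errs. Exchanging the false positives and false negatives leaves kappa unchanged, and its value moves with prevalence even when the error rates are fixed. A moderate kappa could therefore mean that spot urine labels too many people as high consumers, or too few.

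This matters because the proportion with high intake is meant to serve as national baseline data, and Component 4 is the study's only local check on it. A reader given kappa alone could not tell whether the Component 3 proportion is likely to be too high or too low.

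**Working it through.** **The plan's own figures.** The only calculation in Component 4 is the sample size for a correlation, n = 3 + [(1.960 + 0.842) / (atanh r1 − atanh r0)]². Two-sided alpha 0.05 and power 80% are assumed here, because Component 4 states neither; alpha 0.05 and power 80% are the values given for Component 3.
- 0.40 vs 0.65: 3 + (2.802/0.3517)² = 66.5, so 67, as stated.
- 0.40 vs 0.60: 3 + (2.802/0.2695)² = 111.1, so 112, as stated.

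The sample size is not in dispute. It was set for correlation, and no stated figure bears on kappa.

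**Inputs for the check.**
- True prevalence π = 0.67. This is borrowed from the Introduction: "Approximately 67% of individuals exceeded the WHO recommended limit of 2.0 g/day". It comes from Barbados and is an assumption for Jamaica.
- Sensitivity (Se) and specificity (Sp) are illustrative and not taken from the documents.

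**Formulas.**
- Apparent prevalence: q = π·Se + (1−π)(1−Sp).
- Observed agreement: po = π·Se + (1−π)·Sp.
- Chance agreement: pe = π·q + (1−π)(1−q).
- Kappa = (po − pe)/(1 − pe).

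**Similar kappa, opposite error (π = 0.67).**

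| Se | Sp | po | pe | kappa | q | error |
|---|---|---|---|---|---|---|
| 95% | 45% | 0.785 | 0.608 | 0.45 | 82% | +15 points |
| 70% | 82% | 0.740 | 0.510 | 0.47 | 53% | −14 points |

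**An exact tie.** With 120 people, 80 of them high on 24-hour urine (66.7%):
- TP 76, FN 4, FP 24, TN 16: po = 92/120 = 0.767, pe = 0.611, kappa = 0.400. Spot prevalence is 100/120 = 83.3%, an over-call of 16.7 points.
- TP 46, FN 34, FP 4, TN 36: po = 82/120 = 0.683, pe = 0.472, kappa = 0.400. Spot prevalence is 50/120 = 41.7%, an under-call of 25.0 points.

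Sensitivity (95.0% vs 57.5%) and specificity (40.0% vs 90.0%) separate the two tables at once.

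**Symmetry.** Tables (TP, FN, FP, TN) of 70, 5, 25, 20 and 70, 25, 5, 20 both give kappa 0.415.

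**Dependence on prevalence.** With Se = Sp = 80%, kappa is 0.57 at π = 0.67 and 0.35 at π = 0.90.

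**Does the Bland-Altman analysis fill the gap?** Assume normal values with mean 2,656 mg/day (the Barbados mean used in the sample size sections) and 67% above 2,000, which implies an SD of about 1,491. Let the spot estimate have zero mean bias, 60% of that SD, and correlation 0.6 with the 24-hour value. Apparent prevalence is then 77%, sensitivity 88%, specificity 46% and kappa 0.37. The mean difference is zero, yet the proportion is overstated by about 10 points.

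**Precision available.** Take n = 112 (the protocol's own requirement, just under its target of 120) and π = 0.67, giving 75 above and 37 below the limit. Half-width = 1.96·√[p(1−p)/n]:
- Sensitivity 85%: 1.96·√(0.85·0.15/75) = 0.08.
- Specificity 50%: 1.96·√(0.50·0.50/37) = 0.16.

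**Precision of a corrected proportion.** The standard correction is (q + Sp − 1)/(Se + Sp − 1). Its delta-method variance is [q(1−q)·1.94/1,200 + π·Se(1−Se)/112 + (1−π)·Sp(1−Sp)/112] / (Se + Sp − 1)², with Component 3's 1,200 participants and the protocol's design effect of 1.94.
- Se 95%, Sp 45%: (0.00024 + 0.00028 + 0.00073)/0.40², half-width about 17 points.
- Se 70%, Sp 82%: (0.00040 + 0.00126 + 0.00043)/0.52², half-width about 17 points.
- Se 85%, Sp 50%: (0.00032 + 0.00076 + 0.00074)/0.35², half-width about 24 points.

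These widths ignore clustering of the validation sample in about six enumeration districts, and any loss below 112 from the collection-quality exclusions, so they are optimistic.

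**The case against.** The strongest reply is that nothing is stated wrongly. Kappa is a standard measure of classification agreement, which is what the sentence promises. It is a secondary analysis, added after the ICC and Bland-Altman plots. It also cannot be computed without the 2x2 table, from which the other measures are read, and a condensed article may leave these to a fuller plan. This is why the point is a modest one. It still stands as a point about choice: the article names its measure for this comparison, and a better one is available from the same table.

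A reader might infer that the plan is blind to over- and under-estimation, or that it contradicts Objective 4. The documents do not support that. Objective 4 goes on to define the comparison as one of estimates with 24-hour excretion. Bland-Altman plots will show the direction and size of bias in mg/day. Components 3 and 4 also foresee a locally calibrated equation, which addresses systematic bias before anyone is classified. What remains is narrower: neither step gives error rates at the WHO limit, and zero mean bias does not guarantee a correct proportion above it.

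A reader might also want the national proportions in Components 1 and 3 corrected for misclassification. That does not hold up. The half-width of 17 to 24 points exceeds the 14 to 15 point error in the illustration. For Component 1 the transfer itself is unsupported. The validation sample is adults aged 18 or over from the first enumeration districts recruited, with early morning or casual urine. Component 1 is a 2016-2017 survey from age 15 with early morning urine.

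**Conclusion.** The concern holds for the classification analysis only. Kappa is the sole statistic named there, and it cannot show the direction of misclassification. Its symmetry holds at any prevalence. The size shown, kappa of 0.45 to 0.47 with errors of 14 to 15 points in opposite directions, rests on the Barbados 67% and on chosen error rates; it shows what is possible and does not predict the result. Kappa is not wrong to report, the continuous analysis is sound for its purpose, and the sample size reproduces. This is a low-severity improvement that would bring the classification result closer to the stated aim of accuracy.

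**What to change.** In the Component 4 statistical analyses, keep kappa and add the following as the main classification result:
- sensitivity and specificity for intake above the WHO limit, with 95% confidence intervals and 24-hour excretion as the reference;
- the two marginal proportions, spot-based and 24-hour;
- both of these for the PAHO estimate and for any locally calibrated equation.

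State in advance that specificity will be imprecise, at about ±16 points with about 37 people below the limit if prevalence is near 67%. Use the result to say in which direction the Component 3 high-intake proportion is likely to err. Do not require a misclassification-corrected national proportion, and do not carry the error rates to Component 1 without stating the further assumptions this needs.

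The cost is a few lines of analysis and reporting from a 2x2 table that kappa already requires. No new data or participants are needed.
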